### Data Analysis

The data will be stored in a secure server housed in the health system at the University of Alabama at Birmingham and will only be viewed on designated encrypted devices by the principal investigator and study team. Descriptive statistics will be calculated to characterize acceptability and feasibility measures. Stratifying young, Black, sexual minority men by age ranges, 18-21 and 22-29 years, all outcomes will be described by independent variables using frequencies (percentages). Generalized estimated equations will be used to perform logistic regression with empirical standard errors using an exchangeable working correlation, based on the reasonable assumption of equal correlation among members within each index. Other structures will be examined. These models will be used to estimate the rate of PrEP uptake to determine the difference in odds of PrEP uptake, controlling for within-index correlation to determine the difference in the odds of uptake between the two groups (intervention and control). Separate models will be fitted directly after the intervention (*T*_1_) and 3 months following the intervention (*T*_3_). For each model, independent predictor variables (sociodemographic factors, variables related to stigma, knowledge, sexual history and practices, alcohol and substance abuse, and depression and anxiety) will be included as covariates. All categorical outcomes (advancement, change in social capital, connectedness, and condomless anal intercourse in the past 3 months) will be treated similarly. Lastly, if there are overlaps in social networks between index cases, we will perform a network analysis to determine closeness, betweenness, and degree to determine if there will be potential for treatment interference.

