PrEP engagement can be described in terms of discrete stages constituting a PrEP Care Continuum, which includes gaining PrEP awareness, PrEP uptake (linkage to PrEP and PrEP prescription), and PrEP retention (PrEP adherence and PrEP persistence) [15,16]. Previous studies among young, Black, sexual minority men have shown that low perceived risk of HIV acquisition, poor education on sexual health, lack of information on accessing local PrEP services, concerns around PrEP-related costs or insurance, and stigma related to HIV and sexuality act as barriers to PrEP awareness and uptake [17-20]. Additionally, in populations where PrEP uptake is high, barriers to PrEP persistence remain a challenge, including stigma, low perceived HIV risk, PrEP-related side effects, PrEP-related cost, difficulty with adherence to daily medication, and attending regular PrEP-related medical visits requiring routine adjustments and availability of reliable transportation [21-23]. These persisting barriers highlight the need for additional interventions to improve PrEP care engagement.

Much work has been done around targeting social network–level factors in improving PrEP engagement [24,25]. The disproportionate burden of HIV on the young, Black, sexual minority men community in the South has been connected to intersectional stigma, a concept that elucidates how multiple stigmas occurring simultaneously worsen marginalization [26,27]. One social network-level factor that is gaining increased attention is social capital, which refers to “the sum of an individual’s resource-containing, reciprocal, and trustworthy social network connections” [28]. The social capital derived from a social network can be directly influenced by a multitude of factors, including the size and diversity of the social network, as well as knowledge and material resources owned by network members [29,30]. In other words, social networks yield social capital by providing informational, emotional, social, and instrumental support, and are thought to have beneficial effects on health behaviors, such as PrEP use [31].

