#### Recruitment and Sampling

Recruitment of young, Black, sexual minority men occurred in Birmingham, AL, through established connections of the principal investigators (LE in the Birmingham, AL, area and SH in Atlanta, GA); LE and SH have previous experience with recruiting young, Black, sexual minority men for other research studies. When young, Black, sexual minority men were screened in prior studies, respondents were able to indicate if they would like to be contacted for future studies, creating a contact list of HIV-negative young, Black, sexual minority men who are interested in being involved in research. In addition to contacting prior participants, flyers were posted to listservs and physical locations where young, Black, sexual minority men are known to socialize or seek medical care. In addition, the team recruited participants working with Black, sexual minority men study recruiters with large social followings and influence in the community. The eligibility criteria for young, Black, sexual minority men participants were (1) age 18-29 years, (2) cisgender men (based on gender and sex at birth), (3) self-reported past sex with other men (in the past 6 months), (4) Black race, and (5) English speaking. Of note, young, Black, sexual minority men already on PrEP were not excluded. A purposive sampling scheme was used to ensure representation of diverse perspectives of young, Black, sexual minority men. To include both younger and older young, Black, sexual minority men, half of the participants were 18-24 years old, and the other half were 25-29 years old.

Black women for in-depth interviews were recruited by direct referral by young, Black, sexual minority men or CAB members, or from prior studies. This was thought to ensure enrollment of Black women with close connections to young, Black, sexual minority men. Eligibility criteria for Black female participants included (1) Black race, (2) female (cisgender or transgender women), (3) having at least one close connection to a young, Black, sexual minority man, (4) age ≥18 years, and (5) English speaking. Since the aim of these interviews was to explore if certain traits, for example, age, made Black women more suited to lead the discussions, a specific age group within the Black women was not targeted.

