To recruit networks of young, Black, sexual minority men, index young, Black, sexual minority men participants will be recruited first, who will subsequently recruit up to 8 young, Black, sexual minority men members of their own social networks. Similar resources and strategies used earlier will be used to recruit index young, Black, sexual minority men participants. Inclusion criteria for young, Black, sexual minority men index participants are (1) age 18-29 years, (2) HIV negative (based on self-performed HIV OraQuick test), (3) Black cisgender men (based on gender and sex at birth), (4) self-reported past sex with other men (past 6 months), (5) English speaking, and (6) able to identify 6-8 young, Black, sexual minority men in their personal social network. The exclusion criterion is cognitive impairment resulting in the inability to provide consent. Potential index participants will complete a web-based screening survey to determine eligibility. Once an individual is considered eligible, they will be contacted (via phone or in person) to provide more details about the study and will be asked to complete an informed consent. Enrolled index young, Black, sexual minority men participants (n=12) will be randomized (2:1) to the intervention arm (n=30, 6 indices with 5 network members per index) or the control arm (n=30, 6 indices with 5 network members per index). The allocation sequence is generated and assigned by REDCap (Research Electronic Data Capture), and participants are enrolled by our research coordinator. The allocation is computer-generated for randomization by our REDCap. Allocation concealment is provided by the REDCap system. Participants' IDs are provided to our data manager, who enters this information into REDCap. They then inform our research coordinator of the randomization arm for the participant. Both the intervention and control arms will be unblinded. At recruitment, the participants will be educated on the protocol and goal of the study, understanding how support systems can improve access to HIV prevention strategies like PrEP. The randomized controlled trial was registered within ClinicalTrials.gov (NCT07024745).

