#### Intervention Arm

A total of 6 young, Black, sexual minority men's social networks, each including 5 young, Black, sexual minority men (including index participants) and 1 Black female facilitator, will participate in the intervention arm. Before the trainings, the Black female facilitators completed a baseline survey electronically, which measured sociodemographics, HIV knowledge, PrEP knowledge, HIV-related stigma [53], homophobia [54], and PrEP stigma. Black female facilitators have completed their training on app usage. In addition, Black females also completed an (web-based or face-to-face) intensive training covering (1 day) cultural competence and humility when working with sexual and gender minority populations; experiences of stigma among young, Black, sexual minority men in the South; LGBTQ-focused sexual health topics; and basic information about HIV treatment and prevention, including the use of PrEP and steps required to engage in PrEP care.

All young, Black, sexual minority men in the intervention arm will also receive a training (web-based or face-to-face), including a tour of the downloadable US NoW app, a brief demonstration of how to join and participate in the web-based discussion, and practice on posting content publicly and privately. Once trained, young, Black, sexual minority men will complete HIV testing using OraQuick rapid HIV test (remote participants will be asked to text a picture of the test result via a secure server) and an electronic baseline survey prior to study commencement capturing information on sociodemographics, stigma related to race or ethnicity and sexual practices or orientation [55,56], HIV, poverty, PrEP use [57], PrEP knowledge [57], sexual history and practices [58], alcohol [59] and substance abuse [60], and depression [61] and anxiety [62], using appropriate validated measures. In the event an individual tests positive on an HIV test, they will be referred to the linkage team at the study site’s university-affiliated clinic for counseling, access to confirmatory testing, and linkage to care, if necessary.

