##### Secondary Outcomes

The secondary outcomes will include *connectedness to one’s own ethnic community,* measured using an adapted version of the Social Connectedness in the Ethnic Community Scale [66], *condomless anal intercourse in the past 3 months* (ordinal measures), and *PrEP uptake* (yes or no).

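### Baseline PrEP use is collected but left out of the T1 and T3 uptake models, and PrEP uptake is not tied to a new start

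*Protocol article*

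**What the plan says.** **Eligibility.** Recruitment, Screening, and Consent lists six inclusion criteria for index men, ending with "5) English speaking, and (6) able to identify 6-8 young, Black, sexual minority men in their personal social network". The next sentence reads: "The exclusion criterion is cognitive impairment resulting in the inability to provide consent". Nothing there concerns current PrEP use. Network referrals are to be screened (Figure 4 caption), but the article does not give their criteria.

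**Outcome.** Secondary Outcomes lists "and *PrEP uptake* (yes or no") with no reference to baseline status. The only description of the term is in the Introduction: "PrEP uptake (linkage to PrEP and PrEP prescription"). The Introduction treats adherence and persistence as a later stage, retention.

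**Baseline data.** The Intervention Arm section lists "PrEP use [57], PrEP knowledge [57], sexual history and practices [58"] in the baseline survey, so PrEP use is an item separate from knowledge and from sexual history. The Control Arm section says that its surveys are similar.

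**Model.** Data Analysis specifies GEE logistic regression with an exchangeable working correlation, fitted separately at T1 and T3: "These models will be used to estimate the rate of PrEP uptake to determine the difference in odds of PrEP uptake". The covariates are sociodemographics, stigma, knowledge, sexual history, alcohol and substance use, depression and anxiety. PrEP use is not among them, nor in the Independent Variables section.

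**The concern.** A man already on PrEP at baseline has passed the uptake stage as the Introduction describes it. If he enters the T1 or T3 model, his answer measures persistence. The models are separate by time point, so baseline status does not enter as a repeated measure either. Three consequences follow if such men are present:

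- the odds ratio describes a blend of two stages that the article itself distinguishes;
- men who are yes in both arms whatever the intervention does pull the odds ratio toward 1;
- with six networks per arm, a chance difference in baseline use adds noise that the listed covariates do not remove.

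Improving uptake is the stated aim of the intervention, and promising findings are to lead to an application for a fully powered trial. The preliminary uptake estimate would naturally inform that design.

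**Working it through.** **Inputs from the protocol.** 60 men in 12 networks of 5, six networks (30 men) per arm; anticipated uptake 15%; within-index correlation (ICC) 0 or 0.9 (Sample Size Justification). The recruitment section also mentions a 2:1 ratio, but every count given implies equal arms, and equal arms are used here.

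**Assumptions.** The article gives no baseline PrEP prevalence and no effect size. Baseline use b is taken as 0% to 30%. New starts among non-users are 15% (control) and 35% (intervention). All baseline users are still on PrEP at follow-up.

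**1. The plan's own figures.** Margin = 1.96 × √[p(1−p)/n × (1 + (m−1) × ICC)], with n = 60 and m = 5.

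| p | ICC | Formula | Cluster bootstrap (median) | Stated |
|---|---|---|---|---|
| 50% | 0 | ±12.7% | ±12.5% | ±12% |
| 50% | 0.9 | ±27.1% | ±25.0% | ±25% |
| 15% | 0 | ±9.0% | ±9.2% | ±9% |
| 15% | 0.9 | ±19.4% | ±18.3% | ±18% |

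The stated margins are reproduced, using all 60 men.

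**2. Dilution.** Observed proportion = b + (1−b) × start rate. The odds ratio is taken from the two observed proportions.

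| b | Control | Intervention | Difference (points) | Odds ratio |
|---|---|---|---|---|
| 0% | 0.150 | 0.350 | 20 | 3.05 |
| 10% | 0.235 | 0.415 | 18 | 2.31 |
| 20% | 0.320 | 0.480 | 16 | 1.96 |
| 30% | 0.405 | 0.545 | 14 | 1.76 |

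The continuation assumption matters little if continuation is equal in the arms. At b = 20% with 85% continuing, the proportions are 0.17 + 0.80 × 0.15 = 0.29 and 0.17 + 0.80 × 0.35 = 0.45, an odds ratio of 2.00 against 1.96.

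**3. Chance imbalance.** SD of the arm difference in baseline use = √[2b(1−b)/30 × (1 + 4 × ICC)]. At b = 20%:

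- ICC 0: √(0.32/30) = 10.3 points
- ICC 0.3 (assumed): 10.3 × √2.2 = 15.3 points
- ICC 0.9: 10.3 × √4.6 = 22.2 points

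A 10-point difference is therefore unremarkable. With no intervention effect and 15% starts in both arms, baseline use of 20% (intervention) v 10% (control) gives 0.320 v 0.235, an odds ratio of 1.53. The reverse gives 0.65.

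**4. What restricting to non-users costs.** At b = 20%, 48 men remain, about 4 per network. At 15% uptake the margin is 1.96 × √(0.1275/48) = ±10.1% at ICC 0, against ±9.0% with 60 men. At ICC 0.9 it is 1.96 × √(0.1275 × 3.7/48) = ±19.4%, the same as with 60 men, because the networks are smaller. For scale, nominal two-group power with clustering ignored is 0.24 for the mixed outcome (30 per arm, 0.32 v 0.48) and 0.36 for new starts (24 per arm, 0.15 v 0.35).

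**The case against.** Several readings go further than the text.

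- **That the trial is known to admit PrEP users.** A reader may cite "Of note, young, Black, sexual minority men already on PrEP were not excluded". That sentence belongs to the phase 1 interviews. For the trial, the absence of a bar is explicit only for the 12 index men; for the other 48 it is an inference.
- **That all men are in the models and prevalent users count as yes.** Data Analysis names no analysis population. Because the Introduction puts persistence in a later stage, uptake could even mean a new start. The article does not settle it, and a fuller plan may.
- **That men found HIV positive at baseline remain in the denominator.** The article says only that they are referred for confirmatory testing and care.
- **That the estimate is biased by imbalance.** Chance imbalance between randomised arms is extra variance, which a valid confidence interval should reflect.

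It is also fair that the sizes above rest on assumed inputs, that uptake is secondary, and that an undefined outcome called advancement appears in the analysis and might capture movement along the care continuum. All of this limits the point. It does not remove it, because the article commits to a covariate list, and that list omits the baseline value of the outcome although it is collected. That is a stated choice, not a detail left for later.

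**Conclusion.** The point holds in conditional form. The stated criteria do not exclude current PrEP users, uptake is not tied to a new start, and the T1 and T3 models do not adjust for baseline PrEP use. If some men are on PrEP at baseline, the odds ratio mixes persistence with new starts, is diluted, and is less precise than it need be. Under the assumptions shown, 3.05 falls to between 2.31 and 1.76 over 10% to 30% baseline use. If nobody is on PrEP at baseline, nothing changes.

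This should be fixed, but it does not undermine the trial. Uptake is a secondary outcome; the primary outcomes are feasibility, acceptability, social capital and internalised homophobia; and the sample size is justified by feasibility and precision. What is affected is the preliminary efficacy estimate.

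**What to change.** 1. Add baseline PrEP use to the T1 and T3 uptake models, ahead of the long covariate list.
2. Define uptake as a new start since baseline among men not on PrEP at baseline, and report persistence separately for baseline users.
3. Say whether the anticipated 15% refers to all men or to non-users.
4. Report baseline PrEP use by arm and by network.

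No new data are needed. There are three costs:

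- The new-start denominator shrinks by the share already on PrEP; the loss of precision is small, as shown above.
- Baseline PrEP use is self-reported after allocation is known: index men are randomised before referring their networks, the trial is unblinded, and intervention men complete the survey once trained. Restricting to non-users therefore selects on a post-allocation report, which is why its balance by arm must be shown.
- If every baseline user is still on PrEP at follow-up, the covariate separates the logistic model. The new-start analysis then carries the comparison.

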Following enrollment of young, Black, sexual minority men and Black women facilitators, 4 predesignated 60-minute discussions with the network and the Black woman facilitator will commence. Activities of Black female facilitators will include leading discussions and answering any questions or comments posted by young, Black, sexual minority men. Young, Black, sexual minority men participants will be instructed how to use the app throughout the 4-week period. The importance of attendance at the discussions will be emphasized and incentivized through app badges given by other members within the network and by Black female facilitators. Additionally, a reminder, through phone texts, will be sent to young, Black, sexual minority men participants about discussion times.

The data collection began in August 2024 and is expected to be completed in December 2025. Once the intervention ends, young, Black, sexual minority men participants will receive follow-up surveys electronically at *T*_1_ (1-month postintervention) and *T*_3_ (3-month postintervention), capturing the primary and secondary outcomes (explained in detail later). Young, Black, sexual minority men will also be asked to perform a rapid HIV OraQuick test at *T*_3_, remotely. Similarly, Black female facilitators will also complete a follow-up electronic survey at *T*_1,_ which will measure feasibility and acceptability, as well as any changes in stigma and PrEP knowledge or attitudes from baseline. In addition to surveys, Black female facilitators will also participate in web-based qualitative interviews at *T*_3_, which will evaluate PrEP knowledge, intersectional stigma, and change in attitudes following the intervention and gain descriptive information about the process (ie, feasibility and acceptability) of PrEP US NoW facilitation. Additionally, experiences and comfort around delivering the intervention will also be assessed.

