#### Control Arm

The control arm will be similar to the intervention arm in terms of HIV testing, baseline and follow-up surveys, and incentives. However, there will be no Black female facilitators, and instead of the modified intervention HMP app, these participants will use a control version of the HMP app without any discussions or scheduled check-ins with study staff. These participants will, however, be provided with the opportunity to contact the study team in case of technical difficulties or any other issues.

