
While the intervention is expected to be completed within the described timeline, in case young, Black, sexual minority men's networks are not reliably attending the web-based discussions, the intervention may get extended for 5-6 weeks. Although best practices were adopted to design and implement this intervention, there may be a few limitations. For example, there is a potential for selection bias, where young, Black, sexual minority men who are interested in participating in this study may have less internalized stigma than the general population of young, Black, sexual minority men. To avoid this, necessary efforts were made to recruit using web-based approaches and to recruit in rural settings where there was more stigma, leading to fear of unintentional disclosure of sexual orientation through participation in the intervention. Additionally, some young, Black, sexual minority men may be unstably housed or have other disruptions to research participation. To address this, multiple contact methods (email, phone, and social media) will be obtained, and this information will be updated every 3 months.

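### T1 has two definitions, T1 and T3 have no time origin common to both arms, and the 3-month condomless-sex item at T1 reaches back before baseline

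*Protocol article*

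**What the plan says.** The Intervention Arm section has the men using the app "throughout the 4-week period" and ties follow-up to the end of that programme: "Once the intervention ends, young, Black, sexual minority men participants will receive follow-up surveys electronically at" T1, given as "1-month postintervention", and T3, given as "3-month postintervention". The abstract agrees. The Data Analysis section places T1 elsewhere: "Separate models will be fitted directly after the intervention".

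The Control Arm section says controls resemble the intervention arm in testing, surveys and incentives, but use a control app "without any discussions or scheduled check-ins with study staff". The Figure 4 caption lists their surveys at baseline, 1 month and 3 months, and does not say from what date the months are counted.

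Under Anticipated Findings, if networks do not attend the discussions reliably, "the intervention may get extended for 5-6 weeks".

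Among the secondary outcomes are PrEP uptake (yes or no) and "condomless anal intercourse in the past 3 months". The Data Analysis section fits separate models at T1 and T3 and handles the condomless-sex item in the same way as uptake.

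**The concern.** Three things meet at T1 and T3.

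- **Definition.** The section that describes the surveys and the section that fixes the models disagree on when T1 occurs.
- **Origin.** In one arm the clock starts when the discussions end. The other arm has no discussions, so the same rule gives controls no date. A poorly attending intervention network may also have its programme lengthened, which moves its T1 and T3. No corresponding event can occur in a control network.
- **Recall.** A 3-month question asked less than 3 months after baseline counts behaviour from before the trial began.

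If uptake accrues with time, the arm surveyed later shows more of it even with no effect. The recall overlap works the other way and pulls any T1 difference in condomless sex towards zero. The pilot's estimates are meant to inform a fully powered trial, so either distortion could carry into that design.

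**Working it through.** **Inputs from the protocol article.** Programme length 4 weeks; T1 at 0 or 1 month and T3 at 3 months after it ends; recall 3 months; possible extension 5-6 weeks; anticipated uptake 15% (Sample Size Justification). The article states no figure for this point that could be reproduced.

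**Assumptions of this check.** One month = 4.35 weeks, so 3 months = 13.04 weeks. Baseline falls at the start of the 4 weeks, because no gap is stated.

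**1. Survey times, in weeks from the start**

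| Schedule | T1 | T3 |
|---|---|---|
| Intervention, T1 directly after | 4.0 | 17.0 |
| Intervention, T1 one month after | 4 + 4.35 = 8.35 | 4 + 13.04 = 17.04 |
| Controls, if counted from app access | 4.35 | 13.04 |
| Intervention, 5-6 weeks in total (T1 one month after) | 9.3-10.3 | 18.0-19.0 |
| Intervention, 5-6 weeks added (T1 one month after) | 13.3-14.3 | 22.0-23.0 |

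The extension wording can be read as a total of 5-6 weeks (1-2 extra) or as 5-6 extra weeks, so both are shown.

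**2. Effect of unequal follow-up on uptake.** Suppose no true effect, constant accrual and 15% uptake by week 17.04: uptake(t) = 1 - 0.85^(t/17.04). With every intervention network extended and controls surveyed at week 17.04 (odds 0.15/0.85 = 0.1765):

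| Extra weeks | Intervention uptake | Spurious odds ratio |
|---|---|---|
| 1 | 15.8% | 1.06 |
| 2 | 16.6% | 1.13 |
| 5 | 19.0% | 1.33 |
| 6 | 19.7% | 1.39 |

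If only 2 of 6 networks were extended by 5-6 weeks, arm uptake is (4 × 15% + 2 × 19.0%)/6 = 16.3% to (4 × 15% + 2 × 19.7%)/6 = 16.6%, an odds ratio of about 1.11-1.13.

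With no extension, but controls counted from app access, control uptake at T3 is 1 - 0.85^(13.04/17.04) = 11.7%. The odds ratio is 0.1765/(0.117/0.883) = 1.33.

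**3. Recall window at T1.** Pre-baseline share = (13.04 - t)/13.04, and zero if t is 13.04 or more.

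- T1 one month after, t = 8.35: 4.7/13.04 = 36%. A further 4/13.04 = 31% falls during the programme and 4.35/13.04 = 33% after it.
- T1 directly after, t = 4.0: 9.04/13.04 = 69%. If the programme is counted as one calendar month, t = 4.35 and the share is 67%.
- Controls at month 1 from app access, t = 4.35: 67%.
- T3 at 17.04 weeks: the window opens at week 4, so 0%.

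With T1 one month after, the overlap disappears if baseline precedes the first discussion by about 4.7 weeks or more, or if 5-6 weeks are added.

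**The case against.** The strongest reply is that much of this reads bias into silence. Controls do have a nominal schedule, in the Figure 4 caption, and their surveys are described as similar. The exact origin date is a detail an article may leave to the full protocol. A reader might infer that control visits stay put while intervention visits move, but no passage says so; the article does not say how either arm's dates respond to an extension. A reader might also take an odds ratio of 1.3-1.4 as the expected bias. That needs 5-6 added weeks, every intervention network extended, and uptake that accumulates at a constant rate. If the yes/no item means current use, the accrual model need not apply. Even the 4-5 point difference in that case lies within the stated margins for uptake, ±9% to ±18%, and uptake is a secondary outcome of a pilot.

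On recall, one reference period at every wave keeps answers comparable with baseline, the overlap cannot create a false benefit, and sexual history and practices are already listed as covariates.

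These points limit the size and remove the stronger inferences. They do not remove the stated conflict over T1, nor the fact that an end-of-discussions clock and an attendance-triggered extension have no counterpart among controls. They also leave the T1 model of condomless sex partly measuring behaviour before baseline on the planned schedule.

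**Conclusion.** The point holds as a need to reconcile and fix survey timing. The contradiction on T1 is certain and is worth about 4.3 weeks. Unequal elapsed follow-up is possible under the schedule as written, not shown to occur. Under the stated assumptions its effect on the uptake odds ratio is about 1.06-1.13 for a 5-6 week total programme and about 1.3-1.4 for 5-6 added weeks, less if only some networks are extended. It is about 1.33 at T3 if controls are counted from app access with no extension.

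The T1 condomless-sex comparison is diluted towards no effect, with about 36% or 67-69% of its window before baseline according to which T1 applies, if baseline falls at the start of the 4 weeks. It might be inferred that the T3 result for this item is compromised too. It is not: on the planned schedule its window opens as the programme ends.

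**What to change.** 1. Reconcile the Intervention Arm and Data Analysis sections on T1.
2. Time the men's efficacy surveys in both arms at the same number of weeks from network start or randomization, unchanged by any extension. Keep surveys about delivery, such as the facilitators' feasibility and acceptability survey, tied to the actual end of delivery.
3. Base the between-arm comparison of past-3-month condomless sex on T3, adjusted for its baseline value, and do not interpret the T1 model of that item as an intervention effect. The survey item stays as it is, which matters because collection has begun.

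The cost is wording and survey send dates, with one real downside in extended networks. If T1 were fixed at, say, week 8.35, it would fall 2.3-3.3 weeks after the last session of a 5-6 week programme, but 0.7-1.7 weeks before the end of a 9-10 week one, so T1 efficacy results there would reflect partial exposure. A T3 fixed at week 17 would also come sooner after the last session: 1-2 of its 13 recall weeks (8-15%) would cover extended sessions in the first case and 5-6 (38-46%) in the second. Whether to extend the intervention is left to the sponsor.
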